### Statistical Methods

#### Confirmatory Analysis

No confirmatory statistical analysis will be performed. The MTD is determined according to the traditional dose-escalation scheme for Phase I trials in oncology.

#### Descriptive Analysis

Descriptive summary tables will be presented on baseline patient characteristics as well as for all safety parameters by dose level. Absolute and relative frequencies are reported for all toxicities of the CTC list (NCI CTC-AE Version 4.0) by distinguishing the grading and the assessment of the relation to treatment. Within this study, dose limiting toxicities (DLTs) are defined as any grade IV toxicity according to CTCAE Version 4.0 possibly, probably or definitely associated to study treatment during 30 days after completion of therapy.

A description of the individual load of toxicity of each patient will be made separately using individual descriptions eventually supported by graphical methods.

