### Treatment Planning

For particle therapy, patients will be immobilized using an individually manufactured body fixation or positioning device including abdominal pressure plates as described in detail previously [26]. For treatment planning, contrast-enhanced CT (3 mm slice thickness) as well as MR-imaging will be performed for optimal target definition. 4D-CT-imaging is considered standard of care for target definition and for position verification during the course of radiotherapy when treating patients with moving organs. Interstitial fiducial markers are standard of care for treatment planning and patient positioning during treatment and may be implanted prior to radiotherapy within clinical routine.

Organs at risk such as the intestines, stomach, lungs, kidney, spleen and spinal will be contoured. Dose constraints of normal tissue will be respected according to Emami et al. [41].

The Gross Tumor Volume (GTV) will be defined as the area of solid macroscopic tumor contrast enhancement on CT and MR-imaging. The Clinical Target Volume (CTV) will be defined as the GTV plus a margin of 5 mm. The Planning Target Volume (PTV) will include the CTV plus a margin of about 1 cm to account for residual organ motion and setup inaccuracies.

Carbon ion RT planning is performed using the treatment planning software PT-Planning (Siemens, Erlangen, Germany) including biologic plan optimization. Biologically effective dose distributions will be calculated using the α/ß ratio for HCC as well as for the endpoint late toxicity.

No interruptions > 4 days between during study treatment are allowed.

Patient positioning directly prior to particle therapy will be evaluated by comparison of x-rays for static images as well as fluoroscopic imaging to determine residual organ motion in comparison to the DRRs. Set up deviations > 3 mm are corrected prior to radiotherapy.

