### Trial Duration, Schedule and Follow-up

The primary endpoint is acute toxicity of carbon ion radiotherapy observed within 30 days of study treatment.

Patients are scheduled for follow-up visits every 4 weeks after completion of carbon ion radiotherapy for the first 3 months, thereafter in 2-months intervals or as needed clinically including contrast-enhanced MRI as well as thorough clinical-neurological and haematological assessment. These follow-up visits are in line with standard care outside of clinical trials.

The last patient included into the study will be followed for at least 3 months after study treatment. This is considered the final study visit. All other patients will be followed regularly as described in detail until death or until 3 months after LPI.

The overall duration of the trial is expected to be approximately 24 months.

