### Statistical calculations for trial sample size

#### Study hypothesis

The study is designed to demonstrate that carbon ion radiotherapy is safe for the treatment of HCC. The aim of the study is to evaluate the optimal dose tolerated with respect to toxicity.

Unacceptable toxicity (DLT) is defined as any irreversible grade 4 toxicity during a time frame of 30 days as classified by CTCAE version 4.0.

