### Statistical Methods

#### Sample Size Calculation

The calculation of sample size for the PROMETHEUS-01 trial is based on the traditional dose escalation scheme. DLT are considered any irreversible Grade 4 toxicity classified by CTCAE version 4.0 after study treatment.

Patients are treated in cohorts of three each receiving the same dose.

For observation of DLT, patients are observed for 30 days after study treatment. If the last patient of the cohort is observed 30 days after study treatment, patients of the next cohort may be recruited.

If none of the three patients shows a DLT, the next cohort of three patients receives the next higher dose as described above.

Otherwise, if at least one patient of the cohort develops a DLT (1/3), a second cohort of three patients is treated at the same dose level without escalating the dose.

If exactly one out of the six patients (1/6) treated exhibits DLT, the trial continues as planned at the next higher dose level.

If two or more patients out of the six exhibit a DLT, the dose escalation stops at that level and the next lower level is considered as the MTD. When the escalation has stopped, additional patients will be treated at the MTD to a total of nine patients.

This trial is conducted to choose the MTD of carbon ion radiotherapy between five dose levels. Therefore the sample size at maximum is 33 patients (4 dose levels with at maximum 6 patients and 9 patients at the MTD).

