#### Analysis Variables

Primary endpoint is the MTD chosen between the five dose limits based on the traditional dose escalation scheme. Any unpredictable of irreversible grade 4 toxicity possibly, probably or definitely related the study treatment occurring 30 days after completion of study treatment is considered as dose limiting toxicity.

Secondary endpoints are the collection of safety data on the dose levels used in this trial as well as response, progression-free survival, and overall survival.

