#### Analysis Populations

The Analysis set for primary endpoint consists of all patients treated at least once with the study treatment. A total of five analysis sets (one per dose level) will be considered.

Analysis set for secondary endpoints: All patients will be included for analysis for secondary endpoints treated at least one with the study treatment. Additionally, a total of five analysis sets (one per dose level) will be considered to determine any differences in secondary endpoints between the 5 dose levels.

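### The DLT window is fixed inconsistently, and its most explicit statements leave toxicity during the treatment course uncounted

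*Protocol article*

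**What the plan says.** Five sections of the protocol article bear on the window for DLT, or for the primary toxicity endpoint:

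- **Descriptive Analysis** takes any grade 4 event "possibly, probably or definitely associated to study treatment during 30 days after completion of therapy". It does not require the event to be irreversible.
- **Analysis Variables**, which names the MTD as primary endpoint, takes related grade 4 toxicity "occurring 30 days after completion of study treatment is considered as dose limiting toxicity".
- **Sample Size Calculation**, which holds the escalation rule, says "DLT are considered any irreversible Grade 4 toxicity classified by CTCAE version 4.0 after study treatment" and adds "For observation of DLT, patients are observed for 30 days after study treatment".
- **Study hypothesis** says "Unacceptable toxicity (DLT) is defined as any irreversible grade 4 toxicity during a time frame of 30 days as classified by CTCAE version 4.0". The 30 days have no start point.
- **Trial Duration, Schedule and Follow-up** says "The primary endpoint is acute toxicity of carbon ion radiotherapy observed within 30 days of study treatment".

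Two further statements matter. On who is counted, Analysis Populations says "The Analysis set for primary endpoint consists of all patients treated at least once with the study treatment". On the length of the course, Table 1 gives four fractions at every dose step, and Treatment Planning says "No interruptions > 4 days between during study treatment are allowed".

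**The concern.** Every DLT statement with a clear start point begins at the end of treatment. None starts at the first fraction, and none says how to score a patient whose course ends early. Three kinds of event can therefore fall outside the count on a literal reading:

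1. toxicity with onset during the course, because the verb *occurring* in Analysis Variables points to onset within the window;
2. grade 4 toxicity that resolves before the last fraction, which would be eligible under Descriptive Analysis but for the window;
3. toxicity in a course that is never completed, where the event that opens the window in Analysis Variables and Descriptive Analysis does not clearly take place, although the patient remains in the primary analysis set.

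The DLT count in three or six patients is the only input to each escalation decision and to the MTD. An event severe enough to end a course early is one that the count should not be able to lose. Harmonising all sections on a window that starts at completion would make the text consistent and leave this gap open.

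**Working it through.** **The plan's own figure.** Four levels with at most 6 patients and 9 at the MTD: 4 × 6 + 9 = 33. The stated maximum reproduces and does not depend on the window.

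**The statements side by side.**

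| Section | Start of the 30 days | Irreversible required? | Onset during the course |
|---|---|---|---|
| Descriptive Analysis | completion | no | counted only if still present after completion |
| Analysis Variables | completion | qualifier is garbled in the text | not counted if *occurring* means onset |
| Sample Size Calculation | after study treatment | yes | can be counted if still present during observation |
| Study hypothesis | not stated | yes | unclear |
| Trial Duration, Schedule and Follow-up | within 30 days of treatment | not addressed | can be read as included |

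**Effect of one uncounted event under the written rule.**

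- Only event in the first cohort: 1/3 becomes 0/3. The trial escalates at once and the second cohort of three is never treated at that level. With all events counted, that second cohort would have stopped escalation with probability 1 − (1 − p)³, where p is the true DLT rate. This is 1 − 0.512 = 49% at an assumed p = 0.20, and 1 − 0.343 = 66% at p = 0.30.
- One of exactly two events in six, with the other counted in the first cohort: 2/6 becomes 1/6. The trial escalates instead of stopping.
- Six patients with two or more other events counted: it stops either way.
- Only event in what would have been six patients: it escalates either way, although the expansion is skipped.

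**Chance of escalating past one level.** Let m be the share of DLTs not counted, and q = p(1 − m). The rule escalates on 0/3, or on 1/3 followed by 0/3:

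P(escalate) = (1 − q)³ + 3q(1 − q)² × (1 − q)³ = (1 − q)³ + 3q(1 − q)⁵

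The documents give neither p nor m. For illustration I assume p = 0.30, a constant event rate from the first fraction to 30 days after the last, and that every event with onset during the course is missed.

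- Daily fractions: 3 days from first to last, so m = 3/33 = 9%.
- Four treatment-free days in each of the three gaps (days 1, 6, 11, 16): 15 days, so m = 15/45 = 33%.

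| m | q | P(escalate) |
|---|---|---|
| 0 | 0.300 | 0.343 + 0.900 × 0.168 = 0.494 |
| 9% | 0.273 | 0.385 + 0.818 × 0.203 = 0.551 |
| 33% | 0.200 | 0.512 + 0.600 × 0.328 = 0.709 |

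Over a wider range of assumptions:

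| p | m = 0 | m = 25% | m = 50% |
|---|---|---|---|
| 0.20 | 0.709 | 0.814 | 0.906 |
| 0.30 | 0.494 | 0.654 | 0.814 |
| 0.40 | 0.309 | 0.494 | 0.709 |
| 0.50 | 0.172 | 0.351 | 0.600 |

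P(escalate) falls as q rises, so missed events can only raise the chance of escalation.

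**The case against.** A reader might infer that the plan has one settled window opening at completion, that any grade 4 toxicity during the course is therefore not a DLT, and that the dose escalates past it. The documents do not support that much.

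- **The window is not settled.** The follow-up section can be read to include the course, and Study hypothesis has no start point. This objection stands. But it turns a late window into a contradictory one, and the text still needs correcting. The follow-up wording also describes acute toxicity and does not define DLT.
- **Irreversible toxicity persists.** Study hypothesis and the escalation rule restrict DLT to irreversible grade 4 toxicity. Such an event arising in a completed course would still be present afterwards, and could be counted under Descriptive Analysis or under the observation period in Sample Size Calculation. Toxicity that resolves fails the irreversible definition whatever the window. This stands and narrows the gap to the onset reading of Analysis Variables, transient events under Descriptive Analysis, and courses never completed.
- **Scoring an abandoned course as free of DLT is an inference.** No section says so, and completion could be taken to mean the end of treatment for any reason. This stands too. The defect is that the scoring is left open for a patient whom Analysis Populations keeps in the primary set.
- **Escalation past a missed event is not certain.** It depends on the other patients at that level, as shown above.
- **This could be settled when the DLT definitions are reconciled.** Yes, provided that the agreed window does not start at completion.

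**Conclusion.** The point holds as an inconsistently fixed window whose most explicit statements omit the treatment course. It is a fault in stated text about the primary endpoint, not a detail that a condensed article may leave to another document. The direction is certain: uncounted events can only favour escalation and a higher MTD.

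The size is not certain. The rise from 49% to 55%–71% rests on an assumed DLT rate of 0.30, a constant event rate and the premise that every event with onset during the course is missed. The upper end also needs the longest permitted gap at all three intervals. Since persistent irreversible events may well be counted, 71% is an illustrative upper case for this course length, not an estimate. With three or six patients per level, however, one misclassified patient is enough to change a decision in the configurations shown.

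**What to change.** Reconcile Trial Duration, Schedule and Follow-up; Study hypothesis; Sample Size Calculation; Analysis Variables; and Descriptive Analysis on a single endpoint window. State its start, and choose it so that the treatment course is not left uncounted. State whether onset or presence within the window is what counts. In Analysis Populations, state how a patient whose course ends early is scored for DLT, and from which date that patient's 30 days run. Which toxicities qualify clinically is for the trial team; the sections only have to agree.

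The cost is protocol wording. No visit is added and the maximum stays at 33 patients. The small downside is that a level may be declared too toxic slightly more often.

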#### Interim Analyses

Besides the planned analysis during the dose escalation, no further interim analyses are planned.

### Data Handling, Storage and Archiving of Date

According to the §13 of the German GCP-Regulation all important trial documents (e.g. CRF) will be archived for at least 10 years after the trial termination.

According to the §28c of the German X-Ray Regulation (RöV) and the §87 of the German Radiation Protection Regulation (StrlSchV) the informed consent forms including patients' consent for trial participation, application of irradiation and data transmission to the competent authority will be archived for at least 30 years after the trial termination.

The Study Center at the Department of Radiation Oncology Define will be responsible for archiving all relevant data.

#### Good Clinical Practice (GCP)

The procedures set out in this trial protocol, pertaining to the conduct, evaluation, and documentation of this trial, are designed to ensure that all persons involved in the trial by Good Clinical Practice (GCP) and the ethical principles described in the applicable version of the Declaration of Helsinki (2008 Version of the Declaration of Helsinki, adopted at the 59th WMA General Assembly, Seoul, October 2008).

The trial will be carried out in keeping with local legal and regulatory requirements.

#### Ethics, informed consent and safety

A positive Ethics Vote was obtained by the Local Ethics Committee of the medical Faculty at the University of Heidelberg, Germany.

Before study recruitment, a positive vote of the Bundesamt für Strahlenschutz (BfS) has been obtained.

Before being admitted to the clinical trial, the subject must consent to participate after the nature, scope, and possible consequences of the clinical trial have been explained in a form understandable to him or her. The subject must give consent in writing.

#### Treatment at tumor progression

For tumor progression, treatment alternatives will be evaluated and discussed interdisciplinary considering options of surgical resection, systemic treatment such as chemotherapy, a second course of radiation therapy, or other.

## Discussion

Carbon ion radiotherapy offers distinc physical as well as biological benefits and has shown to be a promising treatment alternative for patients with HCC. Previous studies published by Japanese particle therapy centers have shown excellent results with respect to local control as well as overall survival in patients with HCC treated with carbon ion radiotherapy. In the present trial, the Phase I dose escalation concept will evaluated th optimal dose of carbonion radiotherapy for the treatment of HCC when delivered by intensity-controlled rasterscanning.

## Abbreviations

BfS: Bundesamt für Strahlenschutz; CTV: Clinical Target Volume; DLZ: Dose Limiting Toxicity; EC: Ethic's Committee; GCP: Good Clinical Practice; GTV: Gross Tumor Volume; Gy E Gray Equivalent; HCC: Hepatocellular Carcinoma; MTD: Mean tolerable dose; PTV: Planning Target Volume.
